### Outcomes

2.4

The evaluation will be conducted four times, as follows: before the intervention (T0), 2 weeks after the start of the intervention (T2), immediately after the end of the intervention (T4), and 4 weeks after the end of the intervention (T8). There are three outcome measures, as follows: primary, self-reported, and neurophysiological. The SPIRIT participant timeline is shown in Table 1.

**Table 1 tab1:** SPIRIT overview measurements and time points.

	Study period								
		Enrolment	Allocation	Baseline	Intervention	2 weeks	Intervention	4 weeks	8 weeks
Time points				T 0	Week 0–2	T2	Week 2–4	T4	T8

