**Assessments**									
Primary	MRC			Χ		Χ		Χ	Χ
	FMA			Χ		Χ		Χ	Χ
	AROM			Χ		Χ		Χ	Χ
	MAS			Χ		Χ		Χ	Χ
Self-report	SIS			Χ		Χ		Χ	Χ
	SRMS			Χ		Χ		Χ	Χ
	IMI							Χ	
	SoO, SoA							Χ	
Neurophysiology	EEG			Χ		Χ		Χ	Χ
	MEP			Χ		Χ		Χ	Χ

MRC, Medical Research Council; FMA, Fugl-Meyer Assessment; AROM, Active Range of Motion; MAS, Modified Ashworth scale; SIS, Stroke Impact Scale; SRMS, Stroke Rehabilitation Motivation Scale; IMI, Intrinsic Motivation Inventory; SoO, Sense of Ownership; SoA, Sense of Agency; EEG, Electroencephalography; MEP, Motor-Evoked Potential.

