#### Primary outcomes

2.4.1

The MRC scale will be used to test the wrist strength (22). The MRC score ranges from 0 to 5 as follows: grade 0, no visible contraction; grade 1, visible contraction without movement of the limb; grade 2, movement of the limb but not against gravity; grade 3, the movement against gravity over (almost) the full range; grade 4, the movement against gravity and resistance; and grade 5, normal.

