#### Secondary outcomes

2.4.2

We will use the upper extremity of the FMA to assess the motor function of the upper extremity. The FMA evaluates body function encompassing a wide range of assessments. It is highly recommended for evaluating upper extremity function and activity in both research and clinical practice (23). Scores on this assessment range from 0 to 66. We will use the Modified Ashworth scale (MAS) to evaluate muscle spasticity (24). It consists of six points, as follows: 0, no tonus increase; 1, the presence of a catch-and-release feeling at the end of the range of motion or a slight tonus increase in character with minimal resistance; 1 +, there is a slight increase in muscle tone observed through minimal resistance throughout less than half of the joint range of motion; 2, muscle tone is increased throughout the range of motion of the whole joint, but the joints can be moved easily; 3, there is significant tonus increase, which makes passive movement difficult; and 4, the affected parts are rigid in flexion and extension. In addition, we will evaluate the active range of motion in the wrist extension/flexion. The Stroke Impact Scale (SIS) serves as a self-report evaluation for measuring stroke outcomes and is utilized for assessing Health-Related Quality of Life. It assesses eight domains (strength, hand function, mobility, activities of daily living, emotion, memory, communication, and social participation) on a 5-point scale (25). The Korean Version of the Stroke Rehabilitation Motivation Scale (K-SRMS) measures the degree of motivation in patients with stroke during rehabilitation interventions (26). It includes 24 items, and the responses to each item are measured on a scale of 1–5. It is categorized into seven subscales: extrinsic motivation (EM)-introjected (motivation from external factors leading to internal pressures, such as guilt), EM-regulation (motivation from external pressures or rewards, such as praise from others), EM-identification (motivation from activity participation for personal growth), amotivation (AM; absence of motivation), intrinsic motivation (IM)-knowledge (motivation from knowledge gained from the activity), IM-stimulation (motivation from enjoyment or pleasure of an experience), and IM-accomplishment (motivation from personal satisfaction with the activity accomplishment). We will assess the sense of ownership (SoO) and agency (SoA) using questionnaires to understand the experience of BCI in patients. SoO describes the feeling of mindedness toward one’s body parts, feelings, or thoughts. In contrast, SoA refers to the experience of initiating and controlling an action. SoO and SoA are utilized to assess users’ sense of ownership and agency over a virtual limb, as well as to regulate the movements of an artificial hand (27). SoO will be assessed using an 8-statement questionnaire and SoA, using a 16-statement questionnaire; of the 16 questions, eight belong to the FES agency, and the remaining eight belong to the VR agency. It is reported on a 7-point Likert scale ranging from −3 (“totally disagree”) to 3 (“totally agree”), whereby 0 indicates neither agreement nor disagreement (“neutral”). The IMI is a multidimensional measurement device intended to assess participants’ subjective experiences related to a target activity in laboratory experiments (28). It assesses seven subscales: (1) participants’ interest/enjoyment; (2) perceived competence; (3) effort; (4) value/usefulness; (5) felt pressure and tension; (6) social relatedness; and (7) perceived choice while performing a given activity. It is composed of a 45-item questionnaire 7-point Likert scale (ranging from “completely disagree” = 1 to “completely agree” = 7). The SoO and SoA questionnaires and IMI will be assessed only at immediately after the end of the intervention (T4).

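### Table 1 and section 2.4 give a four-measure primary set (MRC, FMA, AROM, MAS), while sections 2.4.1 and 2.4.2 make MRC alone primary; the two must be reconciled before results are known

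*Protocol article*

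**What the plan says.** The article classifies its outcomes in two ways.

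- **Section 2.4 and Table 1.** The introductory sentence reads "There are three outcome measures, as follows: primary, self-reported, and neurophysiological". Table 1 uses the same three classes. Its Primary block holds MRC, FMA, AROM and MAS, each marked at T0, T2, T4 and T8. The next block is Self-report and the last is Neurophysiology. There is no Secondary block.
- **Sections 2.4.1 to 2.4.3.** Under the primary heading there is one measure: "The MRC scale will be used to test the wrist strength". Under the secondary heading come FMA ("We will use the upper extremity of the FMA to assess the motor function of the upper extremity"), MAS ("We will use the Modified Ashworth scale (MAS) to evaluate muscle spasticity") and AROM ("we will evaluate the active range of motion in the wrist extension/flexion"), followed by the questionnaires. Neurophysiological outcomes have their own heading.

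Section 2.11 applies a repeated-measures ANOVA over the four time points to all outcome classes, and its list of classes includes a secondary one. Paired t-tests between time points follow as post-hoc tests. A Bonferroni correction for multiple comparisons is then stated without saying which comparisons it covers. The significance level is 0.05.

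**The concern.** FMA, AROM and MAS are primary in one place and secondary in another, within the same current text. The introduction sets out to establish whether real BCI is superior to sham BCI in subacute stroke, and section 2.11 tests at 0.05. The identity of the primary outcome therefore decides how the result is read.

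Suppose MRC shows nothing and FMA reaches significance. A report could cite Table 1 and call that a positive primary result. If MRC is positive and the rest are not, a report could cite section 2.4.1. A reader could not recognise either as a selective choice, because both versions are published. MRC is also a six-grade scale (0 to 5) applied to patients who enter at grade 2 or below, whereas FMA runs from 0 to 66, so the measures need not give the same answer.

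**Working it through.** **Side by side**

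| Measure | Table 1 block | Section 2.4 sentence | Sections 2.4.1 and 2.4.2 |
|---|---|---|---|
| MRC | Primary | primary class exists | Primary |
| FMA | Primary | no secondary class | Secondary |
| AROM | Primary | no secondary class | Secondary |
| MAS | Primary | no secondary class | Secondary |

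Three of the four measures change class. The section 2.4 sentence agrees with Table 1, so the table label is not an isolated slip in layout. Section 2.11 agrees with the section headings.

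**What the ambiguity is worth**

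The plan states no family-wise error figure and no power calculation, so there is nothing of its own to reproduce. Inputs from the article: four measures in the Primary block, three post-baseline visits (T2, T4, T8), level 0.05. Assumptions: two-sided tests, and all null hypotheses true.

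1. *One overall test per outcome, choice among four.* If independent, 1 − 0.95^4 = 0.1855, or 18.5%.
2. *Bonferroni over the three post-baseline visits within each outcome, choice among four outcomes.* Each test is at 0.05/3 = 0.0167. If all are independent, 1 − (1 − 0.05/3)^12 = 0.183, or 18.3%.
3. *Bonferroni over all six pairs of the four time points instead.* Each test is at 0.05/6 = 0.0083. As if independent, 1 − (1 − 0.05/6)^24 = 0.182. The choice of time-point family makes little difference, because each outcome keeps its own 5%.
4. *Positive correlation.* The article gives no correlations, so a range was assumed and simulated with a multivariate normal model (400,000 draws):

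| Assumed correlation between outcomes | Assumed correlation between visits | Case 2: Bonferroni over visits | Case 1: one test per outcome |
|---|---|---|---|
| 0.3 | 0.5 | 15.8% | 17.4% |
| 0.5 | 0.7 | 12.7% | 15.6% |
| 0.7 | 0.8 | 9.6% | 13.0% |
| 0.8 | 0.9 | 7.2% | 11.4% |

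5. *Bonferroni over outcomes as well.* At 0.05/12 = 0.0042 per test, 1 − (1 − 0.05/12)^12 = 0.049. On this reading the inflation disappears, although the article would still not say which outcome is primary.
6. *MRC alone, with one named time point and contrast.* One test, 5%.

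**The case against.** The strongest reply is that the conflict is largely a labelling error. The headings of sections 2.4.1 to 2.4.3 and the wording of section 2.11 agree on a separate secondary class, with MRC as the only primary outcome. Table 1 and one introductory sentence are the outliers. That is fair as a guide to which version to keep, and the fix follows it. It does not remove the conflict, since both versions are current text. A fuller document that is not shown cannot make both true.

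Three stronger readings are tempting, and the article does not support them.

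- *No error control at all.* Section 2.11 states a Bonferroni correction. What can be said is that its scope is not given.
- *Twelve uncorrected chances of success.* Four outcomes at three visits, each tested at 0.05, would give 1 − 0.95^12 = 46% if independent, and about 32% with outcome correlation 0.5 and visit correlation 0.7. This does not describe the plan. Section 2.11 specifies one ANOVA per outcome and then paired tests between time points, with a Bonferroni correction. Four outcomes by three visits matches no set of tests it lists.
- *The absence of a primary visit as a fault in itself.* A condensed article may leave this to the full protocol or analysis plan. It is worth settling in the same correction, but it does not carry the point.

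It can also be said that this is a pilot trial without a power basis, and that no success rule is written down. That stands as a limit on how much may be claimed. The article nonetheless poses a superiority question and tests it at 0.05, so readers will look for the primary result.

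**Conclusion.** The contradiction is certain and rests on the text alone: the article gives a primary set of four measures in one place and of one measure in another. Its size depends on how the Bonferroni sentence is read. If it covers only time-point comparisons, as its position suggests, choosing among the four outcomes leaves a family-wise error of about 18% under independence. Under the assumed correlations (0.3 to 0.8 between outcomes, 0.5 to 0.9 between visits) it is about 7 to 16%. Independence is unlikely for four measures on the same affected limb, so the lower range is the more plausible guide. If the correction also covers outcomes, the error stays at or below 5% and the remaining problem is selective reporting of which outcome counts as primary. The correction should be made before results are known.

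**What to change.** Change Table 1 and the introductory sentence of section 2.4 to match sections 2.4.1 and 2.4.2. MRC wrist-extensor strength becomes the single primary outcome, FMA, AROM and MAS move to a Secondary block, and the section 2.4 sentence gains a secondary class.

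In the same correction, before results are known, the investigators should:

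- name one primary time point and the between-arm contrast for MRC. T4, the end of the intervention, is a reasonable proposal, but nothing in the article dictates it, so the choice is theirs to make and record;
- state in section 2.11 that the Bonferroni correction covers the time-point comparisons, and that all other outcomes are supportive.

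The work is a table and text correction, with no change to assessments or sample size. What is given up is the option of claiming primary success on FMA, AROM or MAS.

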**Enrolment**									
Eligibility screening		Χ							
Informed consent		Χ							
Allocation			Χ						
**Intervention**									
Experimental					Χ		Χ		
Control					Χ		Χ		
**Assessments**									
Primary	MRC			Χ		Χ		Χ	Χ
	FMA			Χ		Χ		Χ	Χ
	AROM			Χ		Χ		Χ	Χ
	MAS			Χ		Χ		Χ	Χ
Self-report	SIS			Χ		Χ		Χ	Χ
	SRMS			Χ		Χ		Χ	Χ
	IMI							Χ	
	SoO, SoA							Χ	
Neurophysiology	EEG			Χ		Χ		Χ	Χ
	MEP			Χ		Χ		Χ	Χ

MRC, Medical Research Council; FMA, Fugl-Meyer Assessment; AROM, Active Range of Motion; MAS, Modified Ashworth scale; SIS, Stroke Impact Scale; SRMS, Stroke Rehabilitation Motivation Scale; IMI, Intrinsic Motivation Inventory; SoO, Sense of Ownership; SoA, Sense of Agency; EEG, Electroencephalography; MEP, Motor-Evoked Potential.

#### Primary outcomes

2.4.1

The MRC scale will be used to test the wrist strength (22). The MRC score ranges from 0 to 5 as follows: grade 0, no visible contraction; grade 1, visible contraction without movement of the limb; grade 2, movement of the limb but not against gravity; grade 3, the movement against gravity over (almost) the full range; grade 4, the movement against gravity and resistance; and grade 5, normal.

#### Secondary outcomes

2.4.2

We will use the upper extremity of the FMA to assess the motor function of the upper extremity. The FMA evaluates body function encompassing a wide range of assessments. It is highly recommended for evaluating upper extremity function and activity in both research and clinical practice (23). Scores on this assessment range from 0 to 66. We will use the Modified Ashworth scale (MAS) to evaluate muscle spasticity (24). It consists of six points, as follows: 0, no tonus increase; 1, the presence of a catch-and-release feeling at the end of the range of motion or a slight tonus increase in character with minimal resistance; 1 +, there is a slight increase in muscle tone observed through minimal resistance throughout less than half of the joint range of motion; 2, muscle tone is increased throughout the range of motion of the whole joint, but the joints can be moved easily; 3, there is significant tonus increase, which makes passive movement difficult; and 4, the affected parts are rigid in flexion and extension. In addition, we will evaluate the active range of motion in the wrist extension/flexion. The Stroke Impact Scale (SIS) serves as a self-report evaluation for measuring stroke outcomes and is utilized for assessing Health-Related Quality of Life. It assesses eight domains (strength, hand function, mobility, activities of daily living, emotion, memory, communication, and social participation) on a 5-point scale (25). The Korean Version of the Stroke Rehabilitation Motivation Scale (K-SRMS) measures the degree of motivation in patients with stroke during rehabilitation interventions (26). It includes 24 items, and the responses to each item are measured on a scale of 1–5. It is categorized into seven subscales: extrinsic motivation (EM)-introjected (motivation from external factors leading to internal pressures, such as guilt), EM-regulation (motivation from external pressures or rewards, such as praise from others), EM-identification (motivation from activity participation for personal growth), amotivation (AM; absence of motivation), intrinsic motivation (IM)-knowledge (motivation from knowledge gained from the activity), IM-stimulation (motivation from enjoyment or pleasure of an experience), and IM-accomplishment (motivation from personal satisfaction with the activity accomplishment). We will assess the sense of ownership (SoO) and agency (SoA) using questionnaires to understand the experience of BCI in patients. SoO describes the feeling of mindedness toward one’s body parts, feelings, or thoughts. In contrast, SoA refers to the experience of initiating and controlling an action. SoO and SoA are utilized to assess users’ sense of ownership and agency over a virtual limb, as well as to regulate the movements of an artificial hand (27). SoO will be assessed using an 8-statement questionnaire and SoA, using a 16-statement questionnaire; of the 16 questions, eight belong to the FES agency, and the remaining eight belong to the VR agency. It is reported on a 7-point Likert scale ranging from −3 (“totally disagree”) to 3 (“totally agree”), whereby 0 indicates neither agreement nor disagreement (“neutral”). The IMI is a multidimensional measurement device intended to assess participants’ subjective experiences related to a target activity in laboratory experiments (28). It assesses seven subscales: (1) participants’ interest/enjoyment; (2) perceived competence; (3) effort; (4) value/usefulness; (5) felt pressure and tension; (6) social relatedness; and (7) perceived choice while performing a given activity. It is composed of a 45-item questionnaire 7-point Likert scale (ranging from “completely disagree” = 1 to “completely agree” = 7). The SoO and SoA questionnaires and IMI will be assessed only at immediately after the end of the intervention (T4).

#### Neurophysiological outcomes

2.4.3

We will acquire brain signals before and after the intervention to compare the brain activity. Electroencephalography (EEG) signals will be recorded using a 32-channel g.Nautilus system (g.tec Medical Engineering). The electrodes will be placed according to the extended 10–20 international system. The ground channel will be located on the forehead, and the reference channel will be in the right earlobe. The participants will be seated in a comfortable chair. The session will start with preparing and placing electrodes (lasting approximately 30 min) and will continue with resting-state recordings (20 min). We will instruct all participants not to think about anything. We will acquire brain signals with the participants’ eyes closed and eyes open at rest for 5 min twice (20 min).

Cortical excitability will be measured using transcranial magnetic stimulation (TMS) (MagPro stimulator, MagVenture, Lucernemarken, Denmark) at four time points (T0, T2, T4, and T8). During the measurements, the participants will be seated in a comfortable recliner and will hold their hands on their laps in a supine position. The participants will remain silent during the study to avoid speech-induced modulation of cortical excitability. The participants will also be monitored for drowsiness and will be asked to keep their eyes open throughout the motor-evoked potentials (MEP) measurements. A figure-of-8 coil will be employed to stimulate the motor cortex, orienting the coil handle 45° posterior to the midline to ensure perpendicular electromagnetic current flow to the central sulcus (29). The coil will be moved over the scalp in 1-cm increments. For the electromyographic (EMG) signal recording, an active surface electrode will be attached to the contralateral first dorsal interosseous muscle, while reference and ground electrodes will be placed on the index finger’s proximal interphalangeal joint and over the wrist, respectively. Relaxation of the measured muscles will be controlled by continuous visual EMG monitoring. EMG signals will be captured in terms of amplitude and frequency. The “hot spot,” identified as the scalp location yielding the largest MEP amplitude with the lowest stimulation intensity, will be determined (30).

We will assess the resting motor threshold (RMT), defined as the lowest stimulator output intensity eliciting MEPs with an amplitude of at least 50 microvolts in at least five out of 10 consecutive trials (30). We will also examine the MEPs, an electrical signal recorded from the descending motor pathways or muscles following the stimulation of motor pathways within the brain RMT (%). MEP amplitude will be evaluated at 120% of the TMS intensity required to elicit the RMT, and the average peak-to-peak amplitudes of MEPs from 10 consecutive sweeps will be recorded.

We will employ paired-pulse stimulation to assess intracortical inhibition (ICI) and facilitation (ICF) (31). We will initially apply a conditioning stimulus (subthreshold; set at 80% of RMT) and a test stimulus (suprathreshold, set at 120% of RMT) on the affected motor cortex. The MEP values obtained with an inter-stimulus interval of 3 ms will be used to measure ICI and those obtained with an inter-stimulus interval of 10 ms will serve as a measure of ICF. The raw average values for both ICI and ICF will be recorded. Furthermore, we will calculate the ICI and ICF percentages, normalized based on the average MEP obtained with the unconditioned stimuli (set at 120% of the RMT). ICF is a process in which the activity of one neuron facilitates that of another, whereas ICI involves a presynaptic neuron that inhibits the firing of another neuron.

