#### Inclusion criteria

2.2.1

The inclusion criteria are as follows: (1) hemiplegic participants secondary to a first-ever stroke with lesions confined to one hemisphere; (2) subacute stroke, which is defined as motor dysfunction occurring within 1 week to 6 months after stroke onset; (3) Medical Research Council (MRC) scale of affected wrist extensor muscle strength ≦ 2; (4) age > 19 years; and (5) a patient who has the cognitive ability to understand and follow the instructions of the researcher.

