#### Exclusion criteria

2.2.2

The exclusion criteria are as follows: (1) factors impeding recording of electroencephalogram (EEG) signals such as skin infections, scalp wounds, and the presence of metal implants under electrodes; (2) spasticity of wrist flexor, scoring ≥2 on the modified Ashworth scale; (3) cognitive impairments or severe aphasia hindering the ability of the participant to understand and follow the instructions during the research; (4) presence of a neurological or psychiatric disorder other than stroke; (5) musculoskeletal problem or severe pain of the affected upper limb impeding intervention; (6) hemispatial neglect; (7) patients with epilepsy.

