### Statistical methods

2.11

A repeated-measures analysis of variance at the time level (T0, T2, T4, and T8) will be applied to examine whether primary, secondary, and neurophysiology outcomes improved after the intervention. Paired t-tests will be used as post-hoc tests to examine significant changes in different combinations of time points for the scores. The normality of the data will be checked using Kolmogorov–Smirnov tests, and the results will show whether the data are normally distributed. The Bonferroni correction will be used for multiple comparisons.

The Friedman test will be performed for within-group comparisons between time points for non-normally distributed data. The Wilcoxon signed-rank test will also be used for within-group comparisons at each point in time. The resting-state EEG data (with eyes closed) will be first preprocessed to analyze the changes in functional connectivity in the motor area before and after the intervention. The raw EEG data will first be filtered using a 3rd-order Butterworth filter with 1 and 50 Hz cutoff frequencies. Subsequently, it will be divided into 1-s epochs without overlaps. Epochs showing large artifacts, detected using a signal threshold of ±120 μV, will be removed. Next, 30 artifact-free epochs will be randomly chosen for each participant. Partial directed coherence (PDC), a representative effective functional connectivity measure, will be used to evaluate changes in directed functional connectivity from the premotor area to the motor area before and after the intervention (15, 33). Based on the previous study (15), two frequency bands, μ (10–12 Hz) and β (18–24 Hz) bands, will be used for the calculation of PDC. The PDC values will be normalized to a range of 0–1 and then averaged across each participant. Ten consecutive MEPs will be recorded for each stimulus intensity to measure the changes in corticomotor function. These measurements will determine each subject’s average ICI and ICF responses by calculating the mean of 10 trials of paired-pulse TMS. Statistical analyses will be performed using SPSS 21.0 (IBM SPSS Statistics, NY, United States), with the significance level set at *p* < 0.05.

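### MEP amplitude and ICI/ICF have no value without a usable motor threshold, so the four-visit test would describe baseline responders and could not credit a response regained after T0

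*Protocol article*

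**What the plan says.** Section 2.4.3 (Neurophysiological outcomes) defines RMT as "the lowest stimulator output intensity eliciting MEPs with an amplitude of at least 50 microvolts in at least five out of 10 consecutive trials". The other TMS measures are built on it. For amplitude, "MEP amplitude will be evaluated at 120% of the TMS intensity required to elicit the RMT". ICI and ICF use a conditioning pulse at 80% of RMT and a test pulse at 120% on the affected motor cortex, and their percentages are divided by the mean unconditioned MEP at 120% of RMT.

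Section 2.2.1 (Inclusion criteria) admits patients with "Medical Research Council (MRC) scale of affected wrist extensor muscle strength ≦ 2". Neither that list nor the exclusion criteria in 2.2.2 asks for an elicitable MEP. The exclusion nearest to a recording problem concerns the EEG: "factors impeding recording of electroencephalogram (EEG) signals such as skin infections, scalp wounds, and the presence of metal implants under electrodes".

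Section 2.11 (Statistical methods) covers the neurophysiological outcomes with the same test as the others: "A repeated-measures analysis of variance at the time level (T0, T2, T4, and T8) will be applied". Paired t-tests between visits follow as post-hoc tests, and the Friedman test replaces the ANOVA for non-normal data. No section gives a value for an absent MEP or for a 120% intensity beyond the stimulator's range, and no present/absent outcome is defined.

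**The concern.** The trial selects patients with marked distal weakness, then measures corticospinal function with quantities that exist only when the pathway already responds at rest. A patient who has no MEP at T0 and has one at T4 shows a clear neurophysiological gain. Yet that patient has no T0 amplitude from which to compute a change and is not a complete case for the four-visit test.

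The TMS results could then be read as applying to the enrolled population when they describe only patients who responded at baseline and stayed testable. The Discussion presents the EEG and MEP assessments as a route to a fuller evaluation of neuroplasticity. The outcome definition and the test, taken together, leave out one of the changes that such an evaluation should be able to show.

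**Working it through.** **Inputs from the protocol.** 20 patients per arm and 40 in total (2.5, 2.7); visits T0, T2, T4 and T8 (2.4); test intensity 120% of RMT (2.4.3); significance level 0.05 (2.11), taken here as two-sided. **Assumed, because the documents give no figure:** the share of patients without a usable value, equal loss in both arms, and RMT expressed on a 0 to 100% scale of stimulator output.

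**1. The plan's own figure.** 2 × 20 = 40, as stated. Section 2.5 says that no sample size calculation was done, so there is nothing further to reproduce.

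**2. Ceiling on testability.** 1.2 × RMT ≤ 100% requires RMT ≤ 100/1.2 = 83.3%. An RMT of 83% needs 99.6% of output; an RMT of 84% needs 100.8%.

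**3. What exists in which patient at a given visit.**

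| State | RMT | Amplitude at 120% | ICI/ICF percentage |
|---|---|---|---|
| No MEP at any output | undefined | undefined | undefined |
| RMT above 83.3%, up to 100% | valid | not deliverable | not deliverable |
| RMT at or below 83.3% | valid | valid | valid |

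Scoring an absent amplitude as 0 would supply a value in the first row for amplitude. It would not for the ICI/ICF percentages, whose denominator would be 0.

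**4. What the named tests do with gaps.** Classical repeated-measures ANOVA and Friedman both use complete blocks. I checked this on a constructed four-visit data set of 20 subjects, 3 never responsive and 3 responsive only from the third visit. The ANOVA refused the unbalanced data and could be fitted only on the 20 − 3 − 3 = 14 complete subjects, so those who regained a response were lost together with those who never had one.

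Four visits give six pairwise contrasts, three of them with T0. A patient who regains a usable response by T2 contributes to T2–T4, T2–T8 and T4–T8. One who regains it at T4 contributes only to T4–T8. Neither contributes to a contrast with T0.

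**5. Size under assumed rates.** Complete cases = 40 × (1 − u), where u is the share lacking a usable value at one or more visits. The standardized between-arm difference detectable with 80% power is (1.960 + 0.842) × √(2/n), with n per arm.

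| u | Patients left | Per arm | Detectable difference |
|---|---|---|---|
| 0 | 40 | 20 | 0.89 SD |
| 30% | 28 | 14 | 1.06 SD |
| 40% | 24 | 12 | 1.14 SD |
| 50% | 20 | 10 | 1.25 SD |

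The last column only gives a sense of scale, since section 2.11 names no between-arm test. If 40% (16 of 40) had no response at T0 and 25% to 50% of those regained one, 4 to 8 patients would show a recovery that the four-visit test cannot use.

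**The case against.** The strongest reply is that dropping patients is inferred. The article does not say that non-responders are excluded; it leaves open how an unobtainable MEP is coded, and such coding is often left to an analysis plan. If absent amplitude were scored 0, the ANOVA would keep every assessed non-responder and would register a regained response. This stands in part: complete-case loss follows from the named tests and not from stated text. But the article does fix outcomes that have no value in some eligible patients, and zero scoring cannot rescue the ICI/ICF percentages.

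Other limits stand in full:

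- The rate is unknown. Eligibility rests on the wrist extensors, while the recording electrode is on a hand muscle ("an active surface electrode will be attached to the contralateral first dorsal interosseous muscle"). A wrist grade of 0 to 2 does not establish that the hand MEP is absent.
- The affected side is explicit only for ICI/ICF. For RMT and amplitude it is implied by the normalisation. The problem would not arise on the unaffected side.
- An RMT between 84% and 100% is a valid RMT value. Only the measures at 120% are lost.
- These are not primary outcomes; the primary outcome is MRC strength.

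A reader might infer that the arms are no longer comparable. The documents do not support that in general. T0 is measured before training starts, so training cannot affect T0 status, and exclusion on that status narrows the population without by itself unbalancing the arms. A reader might also infer that the hand muscle is the wrong site because the wrist is trained. The protocol contains no contradiction on this; the choice of muscle is a matter of preference.

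**Conclusion.** The point holds as a mismatch between outcome definition, eligibility and test. As written, MEP amplitude and ICI/ICF exist only where an RMT is found and is at or below 83.3% of maximum output. Under the classical four-visit tests the TMS results describe patients who respond at baseline and remain testable, and a response regained after T0 counts neither overall nor against T0.

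Selection that treatment could influence arises only through later visits, when patients who had a usable threshold at T0 lose it or lack it at T2, T4 or T8. The documents give no basis for the size of that group.

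The number affected is likewise not given. With 30% to 50% assumed, 28 to 20 of 40 patients remain. The conclusion rests on the complete-block property of the named tests and on the absence of any stated rule for unmeasurable values. It does not touch the primary outcome. It is worth acting on because the remedy is cheap, and because MEP presence on the affected side must be recorded at the visits to be available later.

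**What to change.** 1. At each visit, record for every patient whether an MEP is present on the affected side, using the protocol's own RMT criterion at any output up to maximum. Compare arms at T4 with adjustment for T0 status.
2. Score amplitude as 0 when no MEP is obtained at maximum output, give an absent RMT the worst rank, and compare arms by ranks. Ranks suit a distribution with a cluster at zero better than the ANOVA does.
3. Write a separate rule for patients whose RMT is measurable but whose 120% intensity exceeds maximum output. They have a response and should not be scored as absent. One option is a rank between absent responses and the lowest amplitude measured at 120%. Whatever rule is chosen should be fixed before the data are seen.
4. Report ICI/ICF percentages descriptively, in responders only, with the number of patients at each visit.
5. State that RMT and amplitude refer to the affected side.

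The cost is analysis wording and one extra yes/no field per visit, from the threshold search already planned. The downside is that presence is coarser than amplitude, so changes among patients who respond throughout are seen only in the rank analysis.
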